### X-ray

All participants will undergo radiographic exams of the knees for the diagnosis of unilateral or bilateral osteoarthritis. Bilateral posterior-anterior weight-bearing semi flexed knee x-rays will be used to identify tibiofemoral OA and skyline views to identify patellofemoral OA [59, 60]. The Kellgren and Lawrence (1956) [56] and American College of Rheumatology criteria will be considered to diagnose and classify KOA, considered as: Grade 0, without changes; Grade I, minimal osteophytes with dubious presence; Grade II/o, defined osteophytes and absence of joint space decrease; Grade II, defined osteophytes and minimal reduction in joint space, grade I in the classification of joint space reduction of Altman and Gold (2007); Grade III, presence of osteophytes and moderate reduction in joint space; Grade IV, significant reduction in joint space and subchondral bone sclerosis [61, 62].

### Thigh computed tomography

Intermuscular adipose tissue of both thighs will be the primary outcome for this study. For this, computed tomography scans will be conducted using a Multislice Tomograph (Brilliance CT 16-slice, Phillips), located at the University Hospital of the Federal University of São Carlos. The exam will be performed by a specialized radiologist.

Image acquisition will be performed as described by Messier et al. (2013) [2]. Participants will be placed supine with their legs held in a neutral position. A 2-dimensional topogram will be obtained from the pelvis to the knees. In order to obtain the scans, the following parameters will be established: helical mode, 120 KV, 150 mAs, with reconstruction of both legs at 5 mm slice thickness and 50 cm display field of view (DFOV).

To establish the site of interest for analysis of thigh composition, the total femur length (from the greater femoral tuberosity to the lower border of the medial femoral condyle) will be transected into three parts. The junction between the proximal and mid-third will be marked for measurement. The area analyzes of thigh composition (interMAT, subcutaneous adipose tissue, and muscle mass) will be manually performed using ITK-SNAP (version 3.6) software, and the area of interest will be selected by a scan according to tissue density attenuation rates for quantification of adipose tissue presented in cm^2^. Additionally, a manual line will be made separating the bony part of the soft tissues, and then the adipose tissue present within the bone area will be subtracted from the area obtained by measuring the interMAT and subcutaneous adipose tissue. Skeletal muscle and adipose tissue areas will be calculated by the range of attenuation values for skeletal muscle (0 to 100 HU) and adipose (− 190 to − 30 HU) tissue [63, 64]. Test-retest reliability on thigh scans re-analyzed 1 week apart was ICC = 0.973 and between evaluators was ICC = 0.986 (*n* = 20).

### Body composition

Dual Energy X-Ray Absorptiometry (DXA, Hologic Discovery A, Bendford, MA) will be used for measurements including lean body mass, body fat mass, and bone mineral density, allowing, therefore, estimation of the total body composition and per body segment.

The scanning will be performed according to the manufacturer’s recommendations. According to the instruction manual, the operator should check that no metal or plastic objects remain in the scanning area, since it may alter the attenuation ratios of the DXA energy [65]. This includes hair clips and pins, snaps, zippers and buttons, jewelry, earrings, bracelets, watches, or rings. The participants will be asked to arrive in a fasted state (at least 4 h) and not to perform any physical activity for 24 h before the exam in order to reduce the biological variability [66].

The participant will be placed in the supine position, in the center of the scanning table, with the head just below the head line marked on the table and remain unmoving during the examination. DXA software will automatically define areas of regional body estimates (left and right arms, legs and trunk) [65]. For this study, it was defined that segment and total body composition areas will be considered to analysis.

### Inflammatory and degradation of articular cartilage biomarkers

Blood samples will be collected in the early morning after a 12-h fast. In total, 4 ml of blood will be collected from the antecubital vein of each participant using a standard procedure heparin-coated vacutainer tube by a specialized laboratory. Participants will be asked to discontinue the use of anti-inflammatories for 72 h prior to collection.

After collection, the blood will remain for 4 h at rest in the refrigerator. Subsequently it will be centrifuged at 1500 rpm for 10 min and the supernatant will be stored as aliquots and frozen at − 80 °C. Serum concentrations of IL-1-β, IL-6, TNF-α, IL-10, leptin, adiponectin, and sCOMP will be measured by the ELISA method (Enzyme-Linked Immunosorbent Assay), according to the manufacturer’s recommendations (Quantikine, R&D Systems, Minneapolis, MN). Patients will be instructed to perform the blood collections in the morning and remain at rest for 30 min [67].

To assess uCTX-II concentration, participants will be instructed not to perform physical activities for 24 h prior to collection, as well as which, urine will be collected in two specific containers (each with a capacity of 80 ml) of the first urine of the day. Participants will be instructed to fill most of the containers provided and keep the containers in the refrigerator (2 to 8 °C) until delivery to the researcher, which should be no more than 2 h after collection. One of the samples will be sent to the laboratory responsible for determining the creatinine concentration, while the other sample will be centrifuged at 3000 rpm for 10 min for homogenization and stored in cryovials for freezing at − 80 °C in a freezer. The procedures will be performed according to the manufacturer’s instructions (Elabscience Biotechnology, Texas, USA) to detect the uCTX-II concentration by the ELISA method.

Samples will be read in a spectrophotometer specific for microplate reading, using a 490 nm filter. The uCTX-II concentration values (ng/L) will be normalized by the total urine creatinine (mmol/L) as well as the correction of uCTX-II concentration unit in ng/mmol [46, 68].

### Questionnaires

#### WOMAC

The WOMAC (*Western Ontario and McMaster Universities*) questionnaire will be used to assess pain, stiffness, and physical function. This is a self-administered instrument that addresses the impact and restrictions specifically in the quality of life of patients with lower limb OA, translated and validated to Portuguese [69]. The WOMAC contains 24 self-reported issues, based on information within 72 h prior to its application, divided into three domains: pain, stiffness, and physical function. Scoring is performed using a Likert scale, wherein each issue scores between 0 and 100, distributed as follows: 0 = none; 25 = mild; 50 = moderate; 75 = intense; and 100 = very intense [69]. The final score will be determined by the maximum score for each domain; the higher the score, the worse the pain, stiffness, and physical function.

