## Methods/Design

### Aim

The main objective of the present study will be to compare the influence of 14-weeks of periodized circuit training with strength training and an educational protocol on thigh interMAT and body composition. Secondarily, the present study will investigate these effects on indicators of cartilage degradation and systemic inflammation, and its repercussions on physical function, pain, and quality of life in patients with knee OA.

Our general hypothesis is that both circuit training and strength training protocols will promote decreases in thigh interMAT, associated with improvement in body composition and muscle strength, and a reduction in inflammatory cytokine concentration (IL1β, IL6, TNF-α), pain, and stiffness in patients with knee OA, leading to consequent improvement in quality of life, compared to the educational protocol. However, it is hypothesized that these benefits, mainly related to the improvement in the body composition and reduction in interMAT will be more evident after the circuit training, compared to the strength training. Additionally, it is also hypothesized that biomarkers of joint degradation may signal exercise efficiency for both groups over the application of both training protocols.

The following methodology is in full agreement with the SPIRIT (Standard Protocol Items for Randomized Trials) recommendations [50–52] [50–52] and the Osteoarthritis Research Society International (OARSI) recommendations for RCTs [53] to ensure methodological rigor. Consolidated Standards of Reporting Trials (CONSORT) [54] guidelines will be followed for reporting the results in a subsequent article.

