#### Pain catastrophizing scale (PCS)

The Pain Catastrophizing Scale is a self-administered scale, easy and fast to apply. This scale will be used to identify individuals with psychological characters for catastrophizing. This instrument consists of 13 items, in which the patient should report the degree of thought or feeling described in relation to pain, always respecting a graduation of 5 points. The total score is given by the sum of all items, ranging from 0 to 52 points. The patients will be asked to answer the questions according to the thoughts and feelings that develop when they are affected by pain, regardless of whether at the moment of the interview the patient is in pain [70].

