#### Application of the periodized circuit training protocol

The circuit training protocol will be conducted in three sessions per week for 14 weeks, totaling 42 exercise sessions. The minimum percentage of sessions that the participants is required to attend is 75% of the total sessions. Each session will consist of: warm-up exercises for 5 min, CT, and cool-down for 5 min with global stretching exercises. Initially, participants will be asked for their perception of pain or discomfort through a visual analogue scale (VAS) and will be instructed to inform the location of the pain through the Nordic questionnaire musculoskeletal symptoms; baseline blood pressure (BPi) and initial heart rate (HRi) will also be measured. Subsequently, the participants will perform a warm-up exercise for 5 min on a stationary bicycle with minimum resistance.

Immediately after the warm-up exercise, each participant will perform the circuit training protocol. The participants will be instructed to perform each exercise as fast as possible, with the maximum number of repetitions during the established time in each training phase (light, moderate, and intense). The first station of exercises to be performed will be defined in a random order at each session. After the end of the first exercise station, the participant will move to the next exercise station, following a specific order to allow different muscle groups to alternate between rest and work, favoring recovery and minimizing the risk of muscle fatigue [34] as shown in Fig. 2.

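### The WOMAC scoring sentence, read literally, reduces each domain to its highest-rated item; it should state a sum or mean with its range

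*Protocol article*

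**What the plan says.** The WOMAC subsection under Questionnaires gives three facts.

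- Structure: "The WOMAC contains 24 self-reported issues, based on information within 72 h prior to its application, divided into three domains", namely pain, stiffness and physical function. The number of items in each domain is not given.
- Item scale: "each issue scores between 0 and 100, distributed as follows: 0 = none; 25 = mild; 50 = moderate; 75 = intense; and 100 = very intense".
- Domain score: "The final score will be determined by the maximum score for each domain", with higher meaning worse. No sum, mean, standardisation or domain range appears.

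The next subsection, on the Pain Catastrophizing Scale (PCS), is explicit: "The total score is given by the sum of all items, ranging from 0 to 52 points".

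On the role of WOMAC, the Aim section lists among the secondary questions "its repercussions on physical function, pain, and quality of life in patients with knee OA". The Thigh computed tomography section states "Intermuscular adipose tissue of both thighs will be the primary outcome for this study". The Statistical analysis section applies a group-by-time ANOVA to the dependent variables and a baseline versus follow-up t-test to WOMAC, after normality checks and transformation where needed.

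**The concern.** This is a rule that the article states, not a detail left to another document. An analyst who follows it as worded would take the highest item in each domain. That score discards most of the information in the items, since it reflects only the worst one and has five levels however many items the domain contains.

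At stake is the trial's patient-reported evidence on pain, stiffness and function. The hypotheses include reduced pain and stiffness and better quality of life, and WOMAC is the only patient-reported pain, stiffness and function measure in the baseline and follow-up battery. The PCS measures catastrophizing. A visual analogue pain rating is used for eligibility and around each circuit session ("participants will be asked for their perception of pain or discomfort through a visual analogue scale (VAS"), but it is not listed among the baseline and follow-up outcomes. With 20 participants per group, a needlessly coarse score can hide a real benefit.

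**Working it through.** **No stated figure to reproduce.** The article gives no WOMAC effect, standard deviation, power or domain range. Its sample size (16 per group, raised to 20) is based on thigh interMAT.

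**1. Attainable values.** Inputs from the article: 24 items, three domains, five levels per item. Assumption: 5, 2 and 17 items for pain, stiffness and function. With k items in steps of 25, a sum or mean has 4k + 1 values and the mean moves in steps of 25/k.

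| Domain (assumed items) | Highest item | Sum or mean | Step of mean |
|---|---|---|---|
| Pain (5) | 5 values | 4×5+1 = 21 | 5 |
| Stiffness (2) | 5 values | 4×2+1 = 9 | 12.5 |
| Function (17) | 5 values | 4×17+1 = 69 | 1.47 |

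**2. Worked example (illustrative).** In a 5-item domain, a patient goes from 100, 75, 75, 50, 50 to 100, 50, 50, 25, 25. The mean falls from 350/5 = 70 to 250/5 = 50, while the highest item stays at 100. The converse also occurs. From 100, 50, 50, 50, 50 to 50 on all five, the mean falls from 60 to 50 but the highest item falls from 100 to 50. The score fails to change only when the unimproved item is the patient's worst.

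**3. Between-arm sensitivity.** Assumptions: one-factor normal model, cut-points −1.2, −0.3, 0.6 and 1.5, inter-item correlation 0.3 to 0.7, latent difference 0.8 SD, 20 per arm, two-sided 5%.

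| Items | Standardised difference, mean | Same, highest item | Power, mean | Power, highest item |
|---|---|---|---|---|
| 2 | 0.52–0.71 | 0.47–0.67 | 38–61% | 32–57% |
| 5 | 0.65–0.76 | 0.52–0.71 | 54–67% | 38–61% |
| 17 | 0.74–0.79 | 0.56–0.72 | 65–70% | 43–62% |

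The standardised difference falls by about 5% (2 items, correlation 0.7: 1 − 0.674/0.706) to 24% (17 items, correlation 0.3: 1 − 0.563/0.741). In those two cases power falls by about 4 points (60.8 to 56.8%) and 22 points (64.9 to 42.9%). In the unimproved arm, 17–25% (5 items) and 28–49% (17 items) score 100 under the highest-item rule, against 1% or less with the mean.

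**4. Sensitivity to within-person change.** Assumptions: same cut-points, latent improvement of 0.6 SD. Inflation = (standardised change with the mean ÷ standardised change with the highest item)².

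- Person variance 50%, perfectly stable severity, identical improvement. Two separate implementations gave, for 5 items, 1.19 against 0.73 (inflation about 2.6) and 1.21 against 0.77 (about 2.4). For 17 items they gave 2.15 against 0.84 (about 6.6) and 2.16 against 0.88 (about 6.1). Squaring the rounded effects shown can move the last digit.
- Stability of severity 0.7 instead of 1: about 1.6 (5 items) and 2.1 (17 items).
- Improvement varying between people with SD 0.6: about 1.5 and 1.7.
- Person variance 70% with stability 0.7: about 1.4 and 1.6.
- Over the wider set of relaxed scenarios: 1.3–2.1 (5 items) and 1.4–3.3 (17 items). A 2-item domain gave about 1.1–1.4 throughout.

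Baseline severity also matters. Varying it within the stable, uniform model gave 2.4–3.0 (5 items) and 5.6–8.8 (17 items).

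**The case against.** The strongest reply is that the article never says highest item. The disputed phrase may be an imperfect description of a domain total, or of a total taken relative to the domain's maximum. The scoring follows a cited, validated Portuguese version that is not at hand. If a total is meant, there is no loss. This stands: the authors' intention cannot be settled from the text. It does not rescue the sentence, because no range confirms a total, the neighbouring PCS text shows that an additive score can be stated plainly, and a third reading (the maximum attainable score) is a constant rather than a patient's score.

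Several stronger conclusions are tempting and are not supported.

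- A reader might infer that the trial will certainly analyse the highest item. The wording permits this but does not establish it.
- A reader might take 2.6 or 6.6 times as the cost. Those figures need perfectly stable severity and the same improvement in everyone, and they shrink sharply when either assumption is relaxed.
- A reader might conclude that the planned parametric analysis breaks down. The heap at 100 depends on assumed cut-points, and the article plans normality checks. Transformation would not remove such a heap, but its presence has not been shown.
- A reader might call the score insensitive. Under the highest-item rule the simulated effects are smaller, but not zero.
- A reader might think that WOMAC alone carries the function conclusion. Three performance-based tests also measure function.

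**Conclusion.** The point holds as a defect in a stated scoring rule. Its wording is ambiguous, and on its literal reading it gives a five-level score driven by the worst item, with reduced sensitivity to change. If a domain total was meant, the loss is nil and only the wording needs repair.

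On the literal reading, and at the central baseline severity simulated, the equivalent inflation in sample size is about 1.3 to 2.6 times for a 5-item domain and 1.4 to 6.6 times for a 17-item domain. A 2-item domain loses little. The item split, inter-item correlation, cut-points, stability of severity and variation in response are all assumptions, so these are ranges and not estimates for this trial.

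Severity is moderate. WOMAC is secondary, the interMAT outcome and sample size are untouched, and the item data allow any scoring. It is still worth correcting, because no other patient-reported measure of pain, stiffness and function is planned at both baseline and follow-up.

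**What to change.** Replace the scoring sentence with: 'Each domain score (pain, stiffness, physical function) is the mean of its items, range 0 to 100 (equivalently the sum divided by the maximum possible sum, times 100); higher = worse.'

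Settle this before the data are analysed, so that the scoring is not chosen with results in view. The cost is one sentence. The scores come from items already collected, and no change to visits, sample size or the primary analysis is needed.

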#### Pain catastrophizing scale (PCS)

The Pain Catastrophizing Scale is a self-administered scale, easy and fast to apply. This scale will be used to identify individuals with psychological characters for catastrophizing. This instrument consists of 13 items, in which the patient should report the degree of thought or feeling described in relation to pain, always respecting a graduation of 5 points. The total score is given by the sum of all items, ranging from 0 to 52 points. The patients will be asked to answer the questions according to the thoughts and feelings that develop when they are affected by pain, regardless of whether at the moment of the interview the patient is in pain [70].

### Performance-based tests

The performance-based tests selected for this study follow the OARSI recommendations for specific purposes of functional capacity evaluation of patients with OA of the knee or hip [71].40 m fast-paced walk test (40 m FPWT)

This test will be conducted to evaluate a short distance walking activity and changing direction during walking. A 10 m walkway will be marked out with bright colored tape at each end. A cone will be placed approximately 2 m before the start mark and 2 m beyond the finish mark of the 10 m walkway for turning. Participants will be instructed to wear comfortable walking footwear (e.g. tennis shoes).

Participants will be asked to walk as quickly but as safely as possible, without running, along a 10 m walkway and then turn around a cone, return, and then repeat the walk again for a total distance of 40 m (3 turns). Regular walking aids will be allowed and recorded. Timing will start on the signal to start at the start line and terminate once the participant crosses back over the start line after completing the 40 m (4 × 10 m). When the participant crosses the 10 m mark, timing will be paused whilst the participant turns around the cone and then resumed once they cross the 10 m mark again. The same will be repeated for the following turns and the timer stopped once the participant crosses the start line for the final time. The time of one trial will be recorded to the nearest 100th of a second and expressed as speed m/s by dividing distance (40 m) by time (s) [71].30 s chair stand test (30s-CST)

This test will be conducted to evaluate the sit-to-stand activity, lower body strength, and dynamic balance. This test will evaluate the maximum number of chair stand repetitions possible in a 30 s period. The back of the chair will be placed against a wall, so the chair does not slide backwards. Participants will be instructed to wear comfortable walking footwear (e.g. tennis shoes). The same chair will be used for all participants, at baseline and follow up assessments. A straight back chair will be used with a 44 cm seat height, without arms.

The participants will sit on the chair in a position that allows them to place their feet flat on the floor, shoulder width apart, with knees flexed slightly more than 90 degrees so that their heels are somewhat closer to the chair than the back of their knees. Participants will be instructed to cross their arms at the wrists and hold them close to the chest (across chest). The tester will stand close to the side of the chair for safety and so they can observe the technique, ensuring that the participant reaches a full stand and full sit position during the test. A practice trial on one slow paced repetition will be performed before testing to check technique and understanding. From the sitting position, the participant will stand up completely with hips and knees fully extended, then sit completely back down, so that their bottom is in full contact with the seat. This will be repeated for 30 s. If the person is not able to stand even once then they will be allowed to place their hands on their legs or use their regular mobility aid. This will be then scored as an adapted test score.

On the signal to begin, the stop watch will be started. The total number of chair stands (up and down equaling one stand) completed in 30 s will be counted. If a full stand has been completed at the end of the 30 s (i.e. standing fully erect or on the way down to the sitting position), then this final stand will be counted in the total. The participant will be allowed to stop and rest if they become tired, but the timer will continue. If the person is not able to stand even once then the score for the test will be zero. If the person is able to stand with adaptions, such as hands placed on their legs, then the number of stands will be recorded as an adapted test score and the adaptations made to the test indicated [71, 72].Stair climb test (SCT)

This test will be conducted to evaluate ascending and descending stair activity, lower body strength, and balance, using a 12-steps flight of stairs with handrails. Each step will measure 16 cm in height and 30 cm in depth, and adequate lighting, free from traffic and external distractions will be ensured. Participants will be instructed to wear comfortable walking footwear (e.g. tennis shoes), and if safety is of concern, the tester will stand behind/below the participant, going up the stairs and ahead/to the side coming down the stairs. If there is no concern for safety, the tester will remain at the start/finish position on the ground landing. A practice trial with the tester standing in the above positions will be conducted to assess safety.

The participant will be instructed to ascend and descend the flight of stairs as quickly as possible but in a safe manner, using the handrail only if needed (if used, this will be recorded). Timing (stop watch) will begin on the signal to start and terminate when the participant returns with both feet to the ground level. The participant can stop and rest if needed but the timer will continue. The total test duration will be timed (in seconds), with longer times indicating more compromised physical function [72].

